## Abstract

**Background:**

The value and utility of self-monitoring of blood glucose (SMBG) in non-insulin treated T2DM has yet to be clearly determined. Findings from studies in this population have been inconsistent, due mainly to design differences and limitations, including the prescribed frequency and timing of SMBG, role of the patient and physician in responding to SMBG results, inclusion criteria that may contribute to untoward floor effects, subject compliance, and cross-arm contamination. We have designed an SMBG intervention study that attempts to address these issues.

**Methods/design:**

The Structured Testing Program (STeP) study is a 12-month, cluster-randomised, multi-centre clinical trial to evaluate whether poorly controlled (HbA1c ≥ 7.5%), non-insulin treated T2DM patients will benefit from a comprehensive, integrated physician/patient intervention using structured SMBG in US primary care practices. Thirty-four practices will be recruited and randomly assigned to an active control group (ACG) that receives enhanced usual care or to an enhanced usual care group plus structured SMBG (STG). A total of 504 patients will be enrolled; eligible patients at each site will be randomly selected using a defined protocol. Anticipated attrition of 20% will yield a sample size of at least 204 per arm, which will provide a 90% power to detect a difference of at least 0.5% in change from baseline in HbA1c values, assuming a common standard deviation of 1.5%. Differences in timing and degree of treatment intensification, cost effectiveness, and changes in patient self-management behaviours, mood, and quality of life (QOL) over time will also be assessed. Analysis of change in HbA1c and other dependent variables over time will be performed using both intent-to-treat and per protocol analyses. Trial results will be available in 2010.

**Discussion:**

The intervention and trial design builds upon previous research by emphasizing appropriate and collaborative use of SMBG by both patients and physicians. Utilization of per protocol and intent-to-treat analyses facilitates a comprehensive assessment of the intervention. Use of practice site cluster-randomisation reduces the potential for intervention contamination, and inclusion criteria (HbA1c ≥ 7.5%) reduces the possibility of floor effects. Inclusion of multiple dependent variables allows us to assess the broader impact of the intervention, including changes in patient and physician attitudes and behaviours.

**Trial Registration:**

Current Controlled Trials NCT00674986.

## Background

Over the past few decades, self-monitoring of blood glucose (SMBG) has been recognized as a core component of effective diabetes self-management [1-4]. This has been supported by a plethora of research that has consistently demonstrated that SMBG is a key contributor to good glycaemic control among insulin-using patients with type 1 (T1DM) [5,6] and type 2 diabetes (T2DM) [7-9]. It remains uncertain, however, whether SMBG is efficacious among the large number of T2DM patients who do not use insulin. Results to date have been decidedly mixed, with some studies pointing to significant glycaemic benefits resulting from SMBG use [10-14], while others have shown no significant benefits [15-18]. Given the costly nature of current T2DM care, especially as the worldwide prevalence of T2DM continues to grow rapidly, it is critical to determine whether resources devoted to SMBG are justified and being applied effectively. Therefore, using randomised controlled trial (RCT) methodology, this study seeks to test the effects of SMBG on metabolic outcomes in insulin naÏve T2DM patients, with special attention devoted to identifying those conditions under which SMBG is or is not beneficial.

This RCT is based on a comprehensive, critical review of the six largest RCTs that included insulin-naÏve T2DM patients [12-14,16-18] and published summaries of the literature [19-22]. Our review suggests that the inconsistent findings found in the literature to date may have resulted from problems in the actual SMBG intervention. These problems point to underlying concerns about the design of future studies, all of which have been raised recently by expert working groups [23,24]. If the actual benefit of SMBG in this population is to be determined definitively, careful attention must be given to these potential limitations; most importantly, we must be certain that the actual SMBG intervention itself is adequate, and that the study design permits a reasonable examination of the research question. Because our study builds upon the previous literature, we raise several questions about major research design and study implementation issues and then show how these issues are addressed in the new study.

### How adequate was the SMBG intervention?

SMBG is only one component of a larger diabetes management regimen. The potential value of SMBG lies in the subsequent actions which may result from its use, including actions that the patient makes directly (e.g., adjusting his/her dietary intake) and/or indirectly (e.g., sharing results with his/her healthcare provider (HCP), who may then recommend treatment changes). Without consideration of this context, efforts to assess any value associated with the simple act of blood glucose monitoring (e.g., the number of blood glucose tests/day) is relatively meaningless. Therefore, we view effective SMBG as a "package" of behaviours, a multi-component intervention that surrounds SMBG actions. In particular, an effective intervention must include three key elements: 1) recommended SMBG frequency and timing (is the prescribed testing regimen sufficiently frequent and comprehensive that meaningful and actionable glucose data can be obtained?); 2) patient response to SMBG results (do patients make use of their SMBG data appropriately?); and 3) HCP use of SMBG results (do HCPs view the SMBG results and make treatment adjustments as needed?). Many SMBG interventions reported in the literature were not comprehensive and were missing key components, thus limiting their potential impact on defined outcomes.

### What is optimal SMBG frequency and timing?

How many blood glucose tests are enough? Should testing take place at specified times during the day to account for postprandial spikes or the impact of other activities? Across the six RCTs, recommended SMBG frequency was 6 - 8 tests/week, with some but not all recommending postprandial testing. Assuming that the purpose is to collect enough data so that patients and/or their HCPs can see recognizable patterns and be confident about taking corrective action, is this frequency and timing sufficient? Most studies, however, do not provide a clear rationale to justify the frequency and timing of testing included in their protocols. Although there are no data that have established a clear threshold for optimal SMBG frequency, there is preliminary evidence suggesting that relatively intensive and structured SMBG, which includes preprandial and postprandial testing over three consecutive days, may be useful [2,23]. Furthermore, this form of intensive monitoring may make it easier for patients to see the glycaemic impact of their own actions, which can enhance their interest and willingness to engage in positive lifestyle changes.

### Do patients make use of SMBG results?

It is often assumed that SMBG functions like other feedback devices (e.g., pedometers) to promote corrective action. If patients do not use SMBG data appropriately, however, then the mere act of blood glucose monitoring may be pointless. Only three of the RCTs we reviewed [12-14] indicated that patients did interpret and respond to their SMBG results. For example, Guerci and colleagues [12] found that the percentage of patients following dietary recommendations remained constant over time in the SMBG arm and decreased significantly in the control arm, suggesting that maintaining dietary adherence was facilitated by the use of SMBG results. Thus, an effective SMBG intervention must include ways to assist patients in making effective use of SMBG data.

### Do HCPs make use of SMBG data?

A key value of SMBG is that it can provide HCPs with the information they need to make timely adjustments in medication and to make focused lifestyle recommendations. When this occurs, it can also help patients to see that their personal efforts to collect SMBG data are worthwhile, thus contributing to patients' ongoing motivation to continue SMBG over time. Nevertheless, two of the six RCTs [17,18] did not provide HCPs with access to SMBG data. Not surprisingly, these RCTs found that SMBG use was not associated with a significant improvement in glycaemic control. In contrast, several other studies provided HCPs with SMBG data to monitor and adjust therapy and as a basis for discussion with patients about their regimen [13,14]. A significant beneficial impact of SMBG was observed in these studies. In sum, these findings suggest that an effective SMBG intervention should include HCPs working closely and collaboratively with their patients, with SMBG data made available to both.

### What is the HbA1c level of patients accepted for study?

Statistically, it would be very difficult to demonstrate improvements in HbA1c due to any intervention if patients are already at or near their target HbA1c levels before the intervention began; there simply would be insufficient room for improvement to occur (floor effect). For example, in the DiGEM [16] trial, significant glycaemic improvement did not occur in any of the three study arms over the one-year period. However, mean HbA1c was 7.5% at baseline, which was at the upper limit of HbA1c targets for T2DM in the United Kingdom. Under such circumstances, neither patients nor HCPs may have been motivated to intensify therapy and, therefore, any favorable impact due to SMBG would have been difficult to demonstrate. It is noteworthy that mean baseline HbA1c was >8.0% in those RCTs that demonstrated a significant HbA1c improvement as a result of SMBG [12-14,17,18]. Therefore, sufficiently high HbA1c levels at baseline are required in RCTs to prevent floor effects from occurring.

### How can intervention contamination across study arms be avoided?

Randomisation of patients within a clinic or practice site was the most commonly used approach among the six RCTs. However, within-practice patient randomisation requires HCPs to become knowledgeable and experienced regarding both the experimental and control protocols, setting the stage for potential contamination, which may reduce differences between the arms of the trial. HCPs may unintentionally make use of the knowledge they acquire working with the intervention group patients to adjust their treatment of control group patients. To avoid this kind of contamination, many studies in primary care employ a cluster-randomisation strategy that randomises practices (not patients) to trial arms [23,24]. This strategy requires that a diverse set of practices is recruited and randomised to each arm. All patients within a given practice are then assigned to a single arm, thus preventing cross-arm contamination.

### Do patients complete the entire protocol as required?

If a substantial percentage of patients or HCPs do not complete the SMBG intervention protocol as required, it will be difficult to evaluate the effects of the intervention fairly. In three of the six RCTs (DiGEM, [16] Drew-King [17], and ESMON [18]) only 48%, 38.5%, and 65%, respectively, of patients completed the prescribed testing requirements. Most studies employed an intent-to-treat analysis to evaluate study findings, which does not account for how well patients actually complied with the study protocol, thus potentially leading to a faulty interpretation of the results. In situations like these, subsequent per protocol analyses may be useful to clarify the impact, if any, of the actual intervention and to explore the reasons why some patients regularly complied with the protocol and others did not. With this knowledge, it is possible to evaluate the effects of the completed intervention and to identify specific patient or disease-related characteristics that are associated with poor SMBG adherence. These can later be used to identify patient subgroups in need of special attention.

### Summary

Due to differences in SMBG intervention protocols and study designs, the value and utility of SMBG in insulin-naÏve T2DM has yet to be determined clearly. Major problems include: comprehensiveness of the prescribed SMBG intervention itself; lack of a rationale for recommended frequency and timing of SMBG; lack of utilization of SMBG findings by patient and HCPs; risk of intervention contamination that can limit between-group differences; floor effects that occur when patients have low levels of HbA1c at baseline; and the low levels of intervention adherence that can affect outcomes. Consequently, we have designed a study that attempts to address each of these problems directly, using a protocol that involves both patients and HCPs in a collaborative and comprehensive SMBG "package."

## Methods/Design

The Structured Testing Program (STeP) Study is a 12-month, cluster-randomised, multi-centre clinical trial to evaluate whether poorly controlled, non-insulin treated T2DM patients benefit from a comprehensive, integrated physician/patient intervention that uses structured SMBG. The study protocol was approved by the Copernicus Group (Central IRB) and is in compliance with the Helsinki Declaration [25].

The primary objective of the study is to determine if an integrated, intensive, and episodic SMBG intervention is associated with a significant reduction in HbA1c over 12 months, compared with enhanced usual care. The study will also examine group differences in: 1) timing and degree of treatment intensification; 2) changes in patient self-management behaviours over time; 3) changes in patient mood and quality of life (QOL) over time; and 4) cost effectiveness of the intervention.

### Hypothesis

The overarching hypothesis is that SMBG will lead to significant improvement in glycaemic control among non-insulin treated T2DM patients when it occurs frequently enough for the detection of actionable glucose patterns, and when patients and their physicians possess the knowledge, skills, and willingness to interpret and make use of SMBG results in a collaborative fashion. More specifically, we hypothesize that episodic, intensive SMBG - when used appropriately for enhancing patient understanding, promoting patient motivation, and initiating/adjusting therapy - will significantly improve long-term blood glucose control in people with poorly controlled (HbA1c ≥ 7.5%), non-insulin treated T2DM. The practical, yet comprehensive, SMBG protocol includes: 1) short periods of intensive SMBG, in which data are recorded on an easy-to-view, paper-and-pencil form, performed at least quarterly; 2) patient and physician training in the effective use of SMBG data; 3) patient presentation of their SMBG data to their physicians for regular review and discussion; and 4) physician review and discussion of SMBG data with their patients, followed by recommendations for therapy change (pharmacologic and non pharmacologic) as needed. The protocol places significant emphasis on the collaborative efforts and relationship between patients and their physicians because both play critical roles in the appropriate utilization of SMBG data.

### Subjects

Thirty-four primary care practice sites in the eastern United States will be identified and recruited for participation in the study. The sites will include both small and large primary care practices, which serve communities with a range of patient education, social class, and ethnicity that reflects the diversity of primary care settings in the US. Each site will then be randomly assigned (cluster-randomised design) via a defined protocol to enhanced usual care (active control group [ACG]) or enhanced usual care with structured testing (structured testing group [STG]). Additional sites may be recruited as needed to ensure enough patients (minimum of 504 enrolled patients) to adequately power the study.

Two hundred thirty-one patients will be enrolled in the ACG, and 273 in the STG, which we estimate will lead to a total of 204 patients completing each arm at 12 months. Differential enrollment of practices and patients will be undertaken initially to account for potential differences in rates of attrition between the two study arms. Each practice will generate a list of all potential study patients who meet age, diagnosis, and HbA1c inclusion criteria from their individual databases or chart review. Participating physicians will review the list and eliminate any subject for medical reasons, as required by many human research committees in the US. Remaining patients will then be randomly selected from the list, using an external, study-defined protocol.

Inclusion criteria are: T2DM for greater than one year that is managed by their primary care physician; age 25 or more years; HbA1c ≥ 7.5-12.0%; treated by diet, exercise, oral diabetes medication, and/or injectable incretin mimetic; read and write English without assistance; and has not participated in any other research protocol within the last 30 days. Exclusion criteria are: T1DM; managed with insulin at the start of study; C-peptide level greater than 0.50 ng/mL; under the care of an endocrinologist or diabetologist; used systemic oral or inhaled steroids more than 14 days within last 3 months; treated with chemotherapy or radiation therapy; plans to relocate or travel extensively during next year; pregnant or breast feeding; and severe depression or other severe psychological conditions.

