**Figure 2 F2:**
[figure not shown]
**Accu-Chek^® ^360° View blood glucose analysis system**.

Physicians and staff in the ACG and STG arms will be informed about the clinical investigational plan, including the rationale for the study, design of the study protocol, subject-related procedures, and use of evaluation questionnaires. Patients in both arms will receive a blood glucose meter (Accu-Chek^® ^Aviva blood glucose meter system, Roche Diagnostics, Indianapolis, Indiana, USA) and will be thoroughly trained in its operation. ACG patients will be instructed to use their meters following their physician's recommendations.

STG physicians and staff will receive training on interpreting the SMBG data provided by the Tool and will be provided with an algorithm that describes various pharmacologic/lifestyle treatment strategies that can be utilized in response to the specific SMBG patterns identified in their analysis of the Tool. STG physicians will be contacted regularly over the 12 months of the study to enhance the consistency of the intervention over time. All physicians will be blinded to all study-collected measures and scales. Point-of-care HbA1c equipment will be provided to all practices to ensure that any differential availability of this equipment does not affect outcomes.

STG clinic staff will conduct one-on-one training sessions with each STG patient to teach the SMBG protocol. This includes instruction in the use of the meter and administration of a DVD instructional program to explain and demonstrate how to complete the Tool, interpret the SMBG data, and make appropriate changes in lifestyle treatments. One-on-one discussions between patients and staff will provide an opportunity to review the content and purpose of the SMBG intervention, discuss what was learned from the DVD, enhance general understanding, personalize SMBG activities, and address questions and concerns.

Study duration will be 12 months, with patient visits occurring at initial screening and baseline, followed by completion of the Tool prior to visits at months 1, 3, 6, 9, and 12. The sequence of visits is described below and presented in Figure 3.

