#### Screening visit

After eligible patients have been identified via study protocol and contacted by mail, they will be invited to attend an initial screening visit at their physician's office. At screening, investigators will describe the study in detail, obtain written informed consent, record demographics, collect relevant medical history/lifestyle activities, perform physical examinations, collect laboratory samples, and document all current medications, including vitamins and supplements. Patients will also complete the STeP questionnaire, which assesses disease management behaviour, mood, quality of life, and diabetes-related self-efficacy, using validated self-report instruments.

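### As described, physicians prune the eligibility list after their practice is randomised, with no stated concealment of the arm, which leaves the trial open to identification bias of unknown direction and size

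*Protocol article*

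**What the plan says.** The Subjects section sets out the steps in this order.

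1. Sites are identified and recruited.
2. "Each site will then be randomly assigned (cluster-randomised design) via a defined protocol to enhanced usual care" or to the same care plus structured testing.
3. Enrolment targets are given by arm: 231 in ACG and 273 in STG, each expected to leave 204 completers.
4. "Each practice will generate a list of all potential study patients who meet age, diagnosis, and HbA1c inclusion criteria", from its own database or chart review.
5. "Participating physicians will review the list and eliminate any subject for medical reasons". The article attributes this step to what many US research committees require.
6. "Remaining patients will then be randomly selected from the list, using an external, study-defined protocol".

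The Abstract has the same order: practices are recruited and randomised, then patients are enrolled and selected. The Procedure section (text after Figure 2) states the extent of physician blinding: "All physicians will be blinded to all study-collected measures and scales". The arm is not among the things concealed. The same section adds that "STG physicians and staff will receive training on interpreting the SMBG data provided by the Tool". At the later Screening visit, "investigators will describe the study in detail, obtain written informed consent".

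**The concern.** Randomising practices balances the practices. It balances the patients only if patients enter the trial by a process that does not depend on the arm. If the physician who strikes names knows the allocation, the lists behind the two arms can be filtered differently, and the enrolled patients can then differ in prognosis for reasons unrelated to the intervention. This is identification bias, a familiar weakness of cluster trials that select patients after allocation.

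A reason for different filtering is plausible. STG patients must complete seven tests a day on three consecutive days (3 x 7 = 21 tests) before visits. The sponsor's own targets also allow for more loss in STG than in ACG. What is at stake is the primary comparison of change in HbA1c.

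**Working it through.** **Step 1: order and concealment.** Assignment, arm-specific targets, list, physician review and draw appear in that order in Subjects, and the Abstract agrees. No section places the list or the review before allocation, and none says that the reviewer is unaware of the arm. Physician blinding covers study measures and scales only, and arm-specific training reveals the arm to STG practices once it starts.

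**Step 2: can a later safeguard repair it?**
- The external draw works on a list that has already been filtered.
- The intent-to-treat population (Analysis of Dependent Variables) starts at the completed baseline visit, so patients struck from the list are never in it.
- The planned attrition analysis starts at screening, so earlier removals fall outside it.
- The mixed model under missing at random deals with missing values of enrolled patients. It does not deal with patients who were never enrolled.

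**Step 3: expected loss by arm, from the plan's targets.**
- ACG: 1 - 204/231 = 11.7%.
- STG: 1 - 204/273 = 25.3%.

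**Step 4: the plan's own power figure.** Inputs from Statistical analysis: difference 0.5, SD 1.5 (already raised from 1.15 for clustering), 204 per arm, two-sided alpha 0.05.
- SE = 1.5 x sqrt(2/204) = 0.149.
- Power by the two-sample t-test (noncentral t) = 91.9%; by normal approximation 92.0%.

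The stated 90% is therefore reproduced, slightly on the safe side. The exact t-test needs 191 per arm, and 204 is about 7% above that.

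**Step 5: size of a shift (assumed values).** Suppose a fraction f of the list is struck in one arm only, and the mean 12-month change of those patients differs by d from that of the patients who remain. The full-list mean is then the remaining mean plus f x d, so striking them shifts that arm by f x d. The documents give neither f nor d.
- f = 10%, d = 0.5: 0.05.
- f = 20%, d = 0.5: 0.10.
- f = 30%, d = 0.5: 0.15.
- f = 20%, d = 1.0: 0.20.

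**Step 6: consequence of a net shift b** (normal approximation, Phi = standard normal distribution function).
- Type I error = 1 - Phi(1.96 - b/SE) + Phi(-1.96 - b/SE).
- Power, if the shift goes against STG = Phi((0.5 - b)/SE - 1.96).

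| Shift b | Share of the 0.5 target | Type I error | Power if against STG |
|---|---|---|---|
| 0 | 0% | 5.0% | 92% |
| 0.05 | 10% | 6.3% | 86% |
| 0.10 | 20% | 10.3% | 77% |
| 0.15 | 30% | 17.3% | 65% |
| 0.20 | 40% | 27.0% | 52% |

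**The case against.** The strongest reply is that the sequence is inferred. In Subjects, one time word links recruitment to assignment and another links the physician review to the draw, but none links assignment to the making of the list. The section is not strictly chronological either: 12-month completers come before the list, and eligibility criteria come last. Different totals by arm are compatible with lists locked beforehand, from which an outside party draws different numbers. Assignment and selection each follow a protocol that is not shown, the study design figure is not available, and an article commonly leaves such detail to the full protocol.

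This stands as a limit on certainty. The article does not say in so many words that the review follows allocation or that the physician knows the arm. The point still goes beyond missing detail, because both places that describe the process give the same order and the stated blinding does not extend to the arm.

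A second reply is that removal is restricted to medical reasons, the starting list covers all potentially eligible patients, and the final draw is external. This also stands in part. Doubt about whether a patient will cope with the Tool is not, on its face, a medical reason, and physicians cannot hand-pick the patients who are drawn. However, the article does not define medical reasons, so the step remains discretionary.

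A reader might infer that the bias favours STG, because only STG physicians have a motive to strike difficult patients. The documents do not support that. ACG patients also face repeated visits, blood samples, questionnaires and meter uploads. The article itself argues, in its section on baseline HbA1c, that higher baseline values leave more room for improvement. If STG physicians struck poorly controlled patients, the shift could go against STG.

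**Conclusion.** The point holds as a weakness of the sequence as described: the review follows allocation, concealment of the arm is not stated, and the external draw protects only what the review leaves. It does not show that biased selection will occur, or in which direction.

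The range of 0.05 to 0.20 HbA1c points, with type I error of about 6% to 27% or power of about 86% to 52%, rests wholly on assumed f and d and on removal in one arm only. The top of the range needs 20% of the list struck in one arm, with a mean change 1.0 point away from the rest, which is 1.0/1.15 = 0.87 of the uninflated SD. It marks an extreme and should carry little weight. Adjustment for baseline factors could reduce imbalance in what is measured, but not in unmeasured factors such as expected adherence.

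This is a cheap improvement worth making. It invalidates none of the plan's sample-size figures. If the full protocol already completes the review before allocation, one sentence saying so would settle the matter.

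**What to change.** Keep the physician review for medical reasons and change when it is done:

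- Each practice generates its list, the physicians complete the review, and a reason is logged for each removal.
- The list is locked and the external party fixes the random draw order before the practice is told its allocation.
- The same order applies to any additional sites recruited later.
- Where a site already knows its arm, removals are logged with reasons.
- Removals and refusals are reported by arm.

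The cost is a short delay before a practice learns its arm and can start training. No sample-size figure changes. The fix does not remove selection at consent, which as described still follows allocation; reporting refusals by arm makes that visible but does not prevent it.

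### As printed, the C-peptide exclusion conflicts with the trial's stated type 2 population; its direction must be reconciled and corrected

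*Protocol article*

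**What the plan says.** The Subjects section opens its exclusion list with "Exclusion criteria are: T1DM; managed with insulin at the start of study" and continues directly with "C-peptide level greater than 0.50 ng/mL". The direction is given in words, so it cannot be a symbol lost in reading the PDF.

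The same section describes who should be enrolled: "T2DM for greater than one year that is managed by their primary care physician", with HbA1c given as "HbA1c ≥ 7.5-12.0" percent, and "treated by diet, exercise, oral diabetes medication, and/or injectable incretin mimetic". The opening of Methods/Design states the aim as to "evaluate whether poorly controlled, non-insulin treated T2DM patients benefit". The Hypothesis section refers to "people with poorly controlled (HbA1c ≥ 7.5%), non-insulin treated T2DM".

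The article mentions C-peptide nowhere else. It gives no reference range and no reason for selecting patients with low values.

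**The concern.** C-peptide is a marker of endogenous insulin production. In a list that also removes type 1 diabetes and insulin-managed patients, one would expect a C-peptide limit to screen out insulin-deficient patients. The printed line does the opposite: it removes patients above the limit, who still make insulin, and leaves those at or below it.

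What is at stake is the published definition of the study population. Anyone who judges generalisability, replicates the trial or pools it with others will take eligibility from this section. A study that followed the line literally would ask its question in a different population from the one in its objective and hypothesis, and would lose most of its candidates after consent and screening.

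**Working it through.** **Direction of the criterion.** No figure in the plan depends on this line, so there is none to reproduce. The first step is to set the criteria side by side (all from Subjects).

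| Criterion | Patients who remain eligible |
|---|---|
| Include type 2 diabetes for more than one year | Established type 2 diabetes |
| Include treatment by diet, exercise, oral agents and/or an incretin mimetic | Managed without insulin |
| Exclude type 1 diabetes | Those without the typically insulin-deficient form |
| Exclude insulin management at the start | Those not on insulin |
| Exclude C-peptide above 0.50 ng/mL (as printed) | C-peptide at or below 0.50 ng/mL, i.e. low own insulin production |

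The first four rows select patients who would be expected to make insulin. The last row selects against them. The criteria are not a formal contradiction, since a patient could satisfy all five, but they do not describe one coherent population.

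**Scale of the effect.** Inputs:

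- Enrolment target N = 504 (Abstract and Subjects).
- Planned practices = 34 (Abstract and Subjects).
- q = share of otherwise eligible patients with C-peptide at or below 0.50 ng/mL. The documents do not give it; 1% to 10% is assumed.

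Formulas, counting losses on the C-peptide criterion only and rounding up:

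- As printed: number screened = N / q
- Direction reversed: number screened = N / (1 − q)

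| Assumed q | As printed | Reversed |
|---|---|---|
| 1% | 504 / 0.01 = 50,400 | 504 / 0.99 = 510 |
| 2% | 504 / 0.02 = 25,200 | 504 / 0.98 = 515 |
| 5% | 504 / 0.05 = 10,080 | 504 / 0.95 = 531 |
| 10% | 504 / 0.10 = 5,040 | 504 / 0.90 = 560 |

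Per planned practice, the printed rule implies between 5,040 / 34 ≈ 148 and 50,400 / 34 ≈ 1,482 patients screened. Reversed, the figures are 510 / 34 = 15 to 560 / 34 ≈ 16. The ratio of the two burdens is (1 − q) / q, which runs from 99 at q = 1% to 9 at q = 10%. Refusals and other screen failures would add to both columns.

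**The case against.** The strongest reply is that this is a misprint in an article, not a fault in the trial. Sites screen from the full protocol, the case report form and the laboratory manual, none of which is shown. A rule that turned away most candidates would have been noticed within weeks. This stands as a limit on what can be claimed. It does not rescue the sentence: the article states the criterion, and states it in a direction that does not fit its own population.

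A second reply is that the size of the effect has no basis in the documents. That is also fair. The conflict rests on the general meaning of C-peptide, and the screening numbers on an assumed q. Nor would the printed rule remove every target patient; those at or below the limit would remain.

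A reader might infer more than the text supports:

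- **That the wrong patients were enrolled, that the target could not be met, or that eligibility differed between practices.** Each requires evidence that sites acted on the printed line, and the article gives none.
- **That the baseline visit enforces this limit.** The Baseline visit section has screening laboratory results checked against the inclusion criteria; it does not name C-peptide, and neither does the Clinical Data section. That the limit would be applied there is a reasonable inference, not a stated fact.
- **That insulin-deficient patients would be kept off insulin for a year.** Subjects bars insulin only at the start of the study, and the Treatment Intensification section counts starting a new medication as a permitted modification.

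**Conclusion.** The criterion is wrong as written. It conflicts with the population in Methods/Design, Hypothesis and the inclusion criteria, and with the two exclusions printed immediately before it. The most likely cause is a reversed inequality, or an inclusion condition that ended up in the exclusion list; the article does not allow a choice between them.

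The conclusion about direction assumes only that C-peptide marks own insulin production and that patients managed without insulin for type 2 diabetes mostly still have it. The size, roughly 9 to 99 times the screening burden of the reversed rule, holds only for an assumed q of 1% to 10%. It illustrates literal use and does not describe what happened. The finding is an error in the stated eligibility rule that must be corrected; it is not evidence that the trial was run on the wrong population.

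**What to change.** 1. Reconcile the C-peptide line in Subjects with the full protocol, the electronic case report form and the laboratory screening flag.
2. Correct its direction so that it agrees with the stated type 2 population, whether as a reworded exclusion or as a condition moved to the inclusion list. The sponsor should confirm its own cut-off and whether a value exactly at the limit is in or out; no value is proposed here.
3. Check the screening records to confirm that no patient was screened in or out under the printed rule. If any were, report how many, by practice and arm.

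The cost is a one-line correction, a check of the eligibility edit in the database and a look through the screening log. It needs no extra patients, visits or procedures.
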